## Abstract

**Background:**

The lungs are involved in up to 70% of cases of leptospirosis. In the more severe forms-bleeding from the lungs and acute respiratory distress syndrome-the lethality is high. The treatment proposed for leptospirotic pneumonitis includes just care for patients in critical condition. Clinical and experimental studies point to the involvement of immunological mechanisms in the physiopathology of lung damage caused by leptospirosis. The aim of this study is to evaluate pulse treatment with methylprednisolone × placebo for leptospirotic pneumonitis.

**Study design:**

This is a randomized double-blind clinical trial to test the efficacy of pulse treatment with methylprednisolone in patients with leptospirotic pneumonitis, compared with a placebo. The patients are recruited from three hospitals in the city of Recife, in the Brazilian State of Pernambuco. The exclusion criteria include patients aged under 15 years, a history of hypersensitivity to the use of corticosteroids, the presence of active infection of fungal, tuberculous or bacterial origin apart from the infection by leptospira itself, the presence of hemoconcentration or atypical lymphocyte count on admission to hospital, the presence of co-morbidities that could be responsible for the radiological and gasometric alterations used to diagnose leptospirotic pneumonitis, evidence of recent cranial trauma, neurosurgery, peptic ulcer, and participation in another clinical trial. The patients are followed until they are discharged from hospital or die. The intervention consists of endovenous pulse treatment with 1 g methylprednisolone for three consecutive days in the study group and a placebo in the control group. The primary end-point is mortality from leptospirotic pneumonitis. The secondary end-points are: evolution of lung disease; the occurrence of nosocomial respiratory infection; duration of mechanical ventilation; duration of intensive care unit (ICU) stay; duration of hospital stay; occurrence of other infection-related complications; other respiratory complications; and adverse effects of methylprednisolone. The study is designed to recruit 266 patients and has a statistical "power" of 80% to detect a 50% reduction in mortality.

**Discussion:**

Lung involvement in leptospirosis is a serious manifestation, with a high and variable mortality rate. There is still no specific clearly-established treatment. Well-designed studies are needed to pave the way towards development of such a treatment.

## Background

Leptospirosis is an acute febrile infectious disease, which is potentially seriously and found all over the world. It is caused by spirochetes of the genus *Leptospira *[1]. In Brazil, it is a serious public health problem [2,3]. Clinical manifestations of leptospirosis are variable, ranging from sub-clinical infection or anicteric and self-limited fever to severe and potentially lethal disease with massive pulmonary hemorrhage or acute adult respiratory distress syndrome (SARA) [3-5]. The lungs are involved in leptospirosis in 16 to 70% of cases in different series and the frequency of such involvement has been on the rise and is becoming the main cause of death from the disease, in Brazil and in other countries [5,6]. Mortality rates for severe lung involvement may be as high as 50% [7]. Current treatment for leptospirotic pneumonitis is restricted to the basic care provided for patients in a critical condition [7,8]. The pathogenesis of such involvement has not yet been clearly established, although knowledge of the physiopathology of leptospirotic pneumonitis suggests the participation of immunological mechanisms in the development of pulmonary forms of the disease [9,10]. Two principal mechanisms have been suggested: vasculitis mediated by toxins and an exaggerated immune response in the host [11-14]. On the basis of evidence that immunological mechanisms are involved in the pathogenesis of lung involvement, high doses or a pulse of dexametasone or methylprednisolone have been used in patients with severe lung involvement in leptospirosis [15-17]. The aim of this article is to describe the design and methods to be used for a randomized double-blind clinical trial to evaluate the use of pulse treatment with methylprednisolone compared with a placebo in patients with lung involvement in letptospirosis.

## Methods/Design

### Study design

The study is a double-blind randomized clinical trial - RCT--which evaluates the efficacy of the use of pulse therapy with methylprednisolone compared to a placebo in patients with lung involvement in leptospirosis. The patients are randomly divided into two clearly-defined groups: a) the study group, which receives conventional treatment associated with endovenous pulse therapy with 1 g methylprednisolone for three consecutive days and b) the control group, which receives the conventional treatment plus a placebo. The patients are followed until such a time as they are discharged from hospital or die. The primary endpoint is taken to be mortality from leptospirotic pneumonitis. The secondary end-points are: a) evolution of lung disease; b) the occurrence of nosocomial respiratory infection; c) duration of mechanical ventilation; d) duration of intensive care unit (ICU) stay; e); duration of hospital stay; f) occurrence of other infection-related complications; h) Other respiratory complications; and i) adverse effects of methylprednisolone.

### Definition of Terms

#### Diagnosis of Leptospirosis

Patients are diagnosed as having leptospirosis when they present epidemiological information relating to contact with flooded areas or professional exposure; clinical criteria include the sudden onset of fever and myalgia; and three of the following laboratory criteria: normal leukometry or leukocytosis, thrombocytopenia, hyperbilirubinemia, increased muscle enzymes and the absence of hyperkalemia. Diagnosis of leptospirosis is confirmed by a serological test (antibody count using the ELISA method) collected after the seventh day and repeated after the tenth day if necessary.

#### Diagnosis of Leptospirotic pneumonitis

Diagnosis of leptospirotic pneumonitis is based on the presence of pulmonary interstitial infiltrate or bilateral alveolar-interstitial infiltrate on chest x-ray, in association with at least one of the following findings: alterations found by lung auscultation (fine crackles), cough, dyspnea, drop in hemoglobin, hemoptoic sputum, hemoptysis and hypoxemia, the latter being defined as a partial pressure of oxygen (PaO_2_) of less than 60 mmHg in arterial gasometry or peripheral saturation of hemoglobin with oxygen (SpO_2_) of less than 90% on pulse oximetry, both under ambient conditions, or an oxygenation índex (relation between PaO_2_/FiO_2_) of <300 mmHg.

### Definition of Variables

#### Independent Variable

The main intervention was the exposure to corticosteroid.

#### Dependent Variables

The dependent variables used to evaluate the primary and secondary outcomes are listed below in Table 1.

**Table 1 T1:** Dependents variables to evaluate the primary and secondary outcomes.

Primary outcome	Mortality
Secondary outcomes	Evolution of lung disease
	Nosocomial respiratory infection
	Duration of mechanical ventilation
	Duration of intensive care unit stay
	Duration of hospital stay
	Occurrence of other infection-related complications
	Other respiratory complications
	Adverse effects of methylprednisolone

#### Mortality

The mortality outcome is defined as death caused leptospirosis related or not to leptospirotic pneumonitis.

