#### Occurrence of other infection-related complications

Occurrence of other infection-related complications may be present when the patient is diagnosed as having infection of the urinary tract, phlebitis, cellulitis, a pulmonary abscess, tracheostomy wound infection, sepsis, septic shock, or fungemia.

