#### Adverse effects of methylprednisolone

Possible adverse effects of methylprednisolone include gastro-intestinal bleeding with a drop in hematometry, fungal infection, Herpes zoster, bacterial infection, hyperglycemia, and systemic arterial hypertension (TA > 149 × 90 mmHg).

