### Sample size

The sample size was calculated on the basis of a statistical significance (alpha error) of 5%, a power of 80%, corresponding to a beta error of 20%. The expected mortality for leptospirotic pneumonitis is 30%. For a reduction of 50% in mortality, the expected mortality in patients treated with corticosteroids would be 15%. The sample size calculated was 133 patients for each group. The same parameters were used to obtain statistical significance and a standard deviation of 21 days for duration of mechanical ventilation, giving an expected sample of 33 patients per group. For the duration of ICU stay variable, the same parameters were used to obtain statistical significance and a standard deviation of 8 days, giving an expected sample of 23 patients per group.

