### Statistical analysis

Double data enter is performed using EPI INFO Version 6.0, giving rise to two datasets that can be compared to detect possible typing errors. The dataset is subsequently checked for consistency. The distribution of potential confounding factors in the two treatment groups are compared to check randomization.

The main analysis will be carried out through comparison of the various outcomes in the two groups, by calculating the percentage distribution and the relative risk. The 95-% confidence interval and the chi-squared test will be used to test statistical association. The t-test will be used to compare the means. The results are considered statistically significant when the p-value is less than 0.05. The efficacy of the intervention is calculated according to the following formula:

Patients randomly included in the study who, for whatever reason, including transfer to another hospital, do not receive the treatment for which they were assigned are considered to belong to the group to which they were allocated **(intention to treat analysis)**. These will be deemed treatment failure. The patients who do not receive confirmation from the laboratory of diagnosis of leptospirosis will still be included in the analysis. They will not be considered as losses or treatment failure. Data analysis will be carried out using EPI INFO Version 6.0 and SPSS 8.0.

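### The primary mortality endpoint carries two different cause-specific definitions, and neither as worded counts a death from a steroid complication

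*Protocol article*

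**What the plan says.** The primary endpoint is described in four places in the protocol article, and the Sample size section gives a planning rate for it.

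- Abstract, Study design: "The primary end-point is mortality from leptospirotic pneumonitis".
- Methods/Design, Study design: "The primary endpoint is taken to be mortality from leptospirotic pneumonitis".
- Definition of Variables, Table 1: the primary outcome is labelled mortality, with no qualifier.
- Definition of Variables, Mortality: "The mortality outcome is defined as death caused leptospirosis related or not to leptospirotic pneumonitis".
- Sample size: "The expected mortality for leptospirotic pneumonitis is 30" per cent, with 15% expected on corticosteroid and 133 patients per group.

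Three other statements bear on which deaths count. The section on adverse effects says: "Possible adverse effects of methylprednisolone include gastro-intestinal bleeding with a drop in hematometry, fungal infection, Herpes zoster, bacterial infection, hyperglycemia". The section on other infection-related complications lists "infection of the urinary tract, phlebitis, cellulitis, a pulmonary abscess, tracheostomy wound infection, sepsis, septic shock, or fungemia". Both sets appear only as secondary outcomes. The Statistical analysis section adds: "The patients who do not receive confirmation from the laboratory of diagnosis of leptospirosis will still be included in the analysis". It does not say how a death in such a patient is classed.

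**The concern.** A primary endpoint needs one event set. Here a leptospirosis death without a pulmonary cause is an event under the Mortality definition and a non-event under the Abstract and Study design. The wording leaves it open which count is primary, and that choice could be made after the data are seen.

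The second problem is common to both definitions. Each is tied to a cause, so each needs a judgement on why a critically ill patient died, and each leaves out deaths judged to have another cause. The protocol itself expects that the study drug may cause bleeding and infection. If the drug causes some deaths in this way, they leave the primary outcome in the treated arm and the comparison tilts towards the drug.

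**Working it through.** **1. Event sets side by side**

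| Death judged due to | Abstract and Study design | Mortality definition | Any cause |
|---|---|---|---|
| Leptospirotic pneumonitis | counted | counted | counted |
| Leptospirosis, not through the lungs | not counted | counted | counted |
| Bleeding or infection not attributed to leptospirosis | not counted | not counted | counted |
| Any cause, leptospirosis never confirmed | not stated | not stated | counted |

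The first definition lies inside the second. They agree on row 1 and differ on row 2. Neither reaches row 3.

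**2. The plan's own sample size**

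Inputs from the Sample size section: p1 = 0.30, p2 = 0.15, alpha 5%, power 80%. A two-sided test is assumed, because sidedness is not stated and the analysis uses a 95% confidence interval. With mean rate p̄ = 0.225:

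n = [1.960·√(2·p̄(1−p̄)) + 0.842·√(p1(1−p1) + p2(1−p2))]² / (p1−p2)² = 120.5

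With continuity correction: n/4 · [1 + √(1 + 4/(n·0.15))]² = 133.5, or 134 after rounding up, against 133 stated. Power at 133 per group is 79.8% with the correction and 83.8% without (80.2% and 84.4% by exact enumeration). The arithmetic is sound. The fault is in the endpoint.

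**3. How far uncounted deaths could tilt the result (assumed inputs)**

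Assume that true mortality is 30% in both arms, that all control deaths are counted, and that a share m of steroid-arm deaths is attributed to another cause and dropped. The analysed rates are 0.30 and p2 = 0.30(1−m), and the apparent relative risk is 1−m. The chance of a significant result favouring the steroid is

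Φ{[(0.30−p2) − 1.960·√(2·p̄(1−p̄)/133)] / √[(0.30·0.70 + p2(1−p2))/133]}

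| m | p2 | Deaths dropped of 39.9 expected | Apparent RR | z | Chance |
|---|---|---|---|---|---|
| 10% | 0.27 | 4.0 | 0.90 | (0.03 − 1.960·0.0554)/0.0553 = −1.42 | 7.8% |
| 20% | 0.24 | 8.0 | 0.80 | (0.06 − 1.960·0.0544)/0.0543 = −0.86 | 19.5% |
| 30% | 0.21 | 12.0 | 0.70 | (0.09 − 1.960·0.0534)/0.0532 = −0.28 | 39.1% |

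Exact enumeration of the uncorrected chi-squared test gives 7.9%, 19.6% and 39.4%. The nominal figure is 2.5%. If some control deaths are dropped as well, the tilt is smaller.

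**4. What an all-cause endpoint does to power at 133 per group (continuity-corrected, exact enumeration)**

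- If 30% and 15% are already all-cause rates: 80%, unchanged.
- If not, and other-cause deaths of 2, 5 or 10 points (assumed) are added equally to both arms, the rates are 32% v 17%, 35% v 20% or 40% v 25%. The relative risk is 0.53, 0.57 or 0.63, and power is 78%, 74% or 70%. The number needed for 80% power is 141, 151 or 165 per group.
- If the steroid alone adds 2, 3 or 5 points of deaths (assumed), the rates are 30% v 17%, 18% or 20%. All-cause relative risk is 0.57, 0.60 or 0.67, while the endpoint as worded still shows 0.50. Power is 66%, 58% or 41%. This loss reflects a smaller true net benefit that the present wording would hide.

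**5. Whether choosing between the two written definitions costs power**

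This depends on what the 30% covers. If it covers all leptospirosis deaths and 90%, 80% or 70% of them (assumed) are from pneumonitis, the narrower endpoint has power of 74%, 68% or 60%. If it covers pneumonitis deaths only, the narrower endpoint keeps its 80% and the wider one gains events. For example, if pneumonitis deaths are two thirds of the total (assumed), the rates are 45% v 22.5% and power is 97%. The documents do not fix the direction.

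**The case against.** The best defence is that every patient enrolled has leptospirotic pneumonitis. Mortality from the condition in the Abstract, Study design and Sample size section may then be shorthand for mortality among such patients, with the Mortality section as the governing definition. That sentence also lacks a word, so its narrowness may be a fault of language. This is a fair account of what the authors may have meant, and the sets are nested rather than irreconcilable. But the text still gives two definitions, and the one said to govern is itself limited to deaths caused by leptospirosis.

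Second, the trial is double-blind and the allocation card is opened only at the end, so knowledge of treatment should not steer the attribution of cause. That stands. It does not stop the drug itself from moving deaths into a cause that is not counted.

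Third, rules for judging cause of death may sit in the full protocol, and their absence from an article is no fault. Such rules would not reconcile two definitions or bring excluded deaths back in.

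Some stronger readings should be resisted:

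- A reader might infer that the trial is underpowered because pneumonitis deaths must fall below 30%. The Sample size section ties the 30% to leptospirotic pneumonitis, and power could move either way.
- A reader might equally take the 30% to be all-cause. Nothing in the text says so.
- The list of infection-related complications should not be read as a list of steroid harms. Only the adverse-effects section attributes effects to the drug.
- The documents do not show that a sepsis death during a leptospirosis admission would be excluded, only that the wording allows it.
- They also do not show that early deaths will go unconfirmed. Serology is taken after the seventh day, but the day from which this is counted is not given.

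**Conclusion.** The point holds in this form: the primary endpoint is stated inconsistently, both versions are cause-specific, and the wording lets deaths from named possible drug effects fall outside the primary outcome. The primary result depends on this definition, so it should be corrected.

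The inconsistency and the exclusion are plain on the page and rest on no assumption. The size of any bias cannot be derived from the documents. The 8%, 20% and 39% false-positive chances rest on equal true mortality of 30%, full counting of control deaths, and assumed shares of uncounted steroid-arm deaths. They show that a handful of reclassified deaths, roughly 4 to 12 of about 40, would matter. They do not predict that this will happen.

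**What to change.** Before unblinding, state one primary endpoint in the Abstract, Study design, Table 1 and Mortality sections: death from any cause, from randomisation over the follow-up already stated (to discharge or death), in all randomised patients whether or not serology confirms leptospirosis. Keep pneumonitis-related death as a secondary outcome. This removes the attribution of cause from the primary analysis and settles the status of deaths in unconfirmed patients.

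In the Sample size section, state which deaths the 30% planning rate covers. If it is already all-cause, the planned power of about 80% stands. If it is not, restate the power. Other-cause deaths of 2 to 10 points, equal in both arms, would put it at about 78% to 70% with 133 per group.

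No new data are needed, because patients are already followed to discharge or death. The cost is an amendment, possibly a modest dilution of the effect by unrelated deaths, and a somewhat less favourable stated power. If the drug does cause deaths, the all-cause effect and its power will be smaller, as they should be.

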#### Evolution of lung disease

The evolution of leptospirotic pneumonitis is evaluated by way of lung auscultation, radiological evaluation, gasometric evaluation and hematometry (hematocrit and hemoglobin) on a daily basis up to the seventh day and then on the 14th and 28th days. Respiratory auscultation is used to determine the presence of crackles. Once these have been identified, their severity is classified according to the extent of lung involvement (Table 2).

**Table 2 T2:** Extent of lung involvement on respiratory auscultation

Severity of lung involvement	Extent of lung involvement on respiratory auscultation
Slight	Lower third
Moderate	Lower two thirds
Severe	Whole lung

A lung auscultation is carried out again on the fifth day of the patient's follow-up and categorized according to whether it is improving or worsening. It is considered to be improving when there is a reduction in the parameters described above and considered to be worsening if there is no change or if there has been an increase in the parameters.

The radiological evaluation aims to determine the presence and the extent of pulmonary infiltrate. When present, it is categorized according to its extent and severity (Table 3).

**Table 3 T3:** Extent of lung involvement according to radiological examination

Severity of lung involvment	Extent of lung involvement according to radiological examination
Slight	Lower third
Moderate	Lower two thirds
Severe	Whole lung

Another radiological examination is carried out on the fifth day of the patient's follow-up and categorized as improving or worsening. It is considered to be improving when there is a decline in the radiological parameters described above. It is considered to have worsened when the parameters have remained unchanged or seen an increase.

In the gasometric evaluation the relation between PaO2/FiO2 is used in order to establish whether there has been an improvement or a decline. It is measured again on the fifth day and categorized as having improved when the value is equal to or greater than 300 and as having declined when the value is less than 300.

The evolution of hematometry is measured by way of hematocrit and hemoglobin levels and considered when there is a decrease of over three percentage points in hematocrit and 1 g/dl in hemoglobin, with no evidence of blood loss. The intensity of bleeding from the lungs is categorized as slight, when the hematocrit loss is more than three and less than five percentage points, moderate when greater than five but less than ten percentage points, and severe when it is greater than ten percentage points. The evolution of hematometry is evaluated on the fifth day of the patient's follow-up and is categorized as having improved when there has been no drop in hematometry or when it is kept in levels considered acceptable, when blood transfusion is necessary. It is considered to have declined when the hematometry remains unchanged after hemotransfusion or when there is an increased drop in hematometry.

Patients are considered to have improved, irrespective of the extent of the improvement, when, after five days of follow-up, there has been an improvement in three of the four parameters evaluated: lung auscultation, radiological evaluation of pulmonary infiltrate, arterial gasometry and hematometry. Improvement is considered to be early when it occurs within the first forty-eight hours and late when it occurs later than this. Treatment is considered to have failed when the patient does not show improvement in three of the four parameters listed above.

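### Evolution of lung disease: the fixed PaO2/FiO2 cut at 300, the auscultation rule and the overlapping hematometry clauses misclassify some patients according to their signs at entry

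*Protocol article*

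**What the plan says.** All references are to the protocol article.

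- **Entry** (Diagnosis of Leptospirotic pneumonitis): a lung infiltrate is mandatory, "in association with at least one of the following findings: alterations found by lung auscultation (fine crackles), cough, dyspnea, drop in hemoglobin", with hypoxemia among the further alternatives. Neither crackles nor a PaO2/FiO2 below 300 is required.
- **Gasometry** (Evolution of lung disease): of the PaO2/FiO2 ratio the article says: "It is measured again on the fifth day and categorized as having improved when the value is equal to or greater than 300". Any lower value counts as a decline.
- **Auscultation** (same section): "It is considered to be improving when there is a reduction in the parameters described above", and it is "considered to be worsening if there is no change or if there has been an increase in the parameters". The X-ray rule follows the same pattern.
- **Hematometry** (same section): improved if there is no drop, or if the level is "kept in levels considered acceptable, when blood transfusion is necessary". The opposite verdict reads: "It is considered to have declined when the hematometry remains unchanged after hemotransfusion", or when the drop increases.
- **Composite** (same section): a patient has improved if three of the four items have improved after five days; otherwise treatment has failed.
- **Schedule**: the four items are assessed daily to day 7, then on days 14 and 28.

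**The concern.** The gasometry item is meant to show whether gas exchange got better or worse, but it records only which side of 300 the patient is on at day 5. Because entry does not fix the starting side, the label can contradict the direction of change. The auscultation item has the converse problem. It is defined by change, but a patient with no crackles has nothing to reduce, and no change counts against the patient. The hematometry item gives two verdicts for one situation and leaves the acceptable level undefined.

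This composite is the first-listed secondary outcome and also the article's definition of treatment failure. One item can decide a 3-of-4 result. At stake are how clearly this outcome separates the arms and whether two assessors would classify the same patient alike.

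**Working it through.** The article states no planning figure for this outcome, so there is none to reproduce. Its 133 per group (mortality 30% v 15%, alpha 5%, power 80%) is used below only as the arm size. A two-sided calculation with continuity correction gives 134, one away from it.

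**Step 1. Apply the rules as written to example patients (values assumed).**

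| Patient | Auscultation | X-ray | Gasometry | Hematometry | Result |
|---|---|---|---|---|---|
| 450→310, crackles unchanged, X-ray one grade better, no drop | no | yes | yes | yes | 3 of 4, improved |
| As above, X-ray unchanged | no | no | yes | yes | 2 of 4, failed |
| 90→290, crackles one grade better, X-ray unchanged, no drop | yes | no | no | yes | 2 of 4, failed |
| As above, X-ray also better | yes | yes | no | yes | 3 of 4, improved |
| No crackles at either time, X-ray better, 150→290, no drop | no | yes | no | yes | 2 of 4, failed |
| No crackles at either time, X-ray better, 400→400, no drop | no | yes | yes | yes | 3 of 4, improved |

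Judged by direction of change, gasometry would be *no* in the first row (a fall of 140) and *yes* in the third (a rise of 200). Both overall results would reverse: the first to 2 of 4, the third to 3 of 4. Rows 2 and 4 show that the composite sometimes absorbs the error.

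**Step 2. Hematometry.** Take a transfused patient whose values stay unchanged at a level judged acceptable. The first transfusion clause says improved, the second says declined. If exactly two other items improved, the total is 3 of 4 (improved) or 2 of 4 (failed), depending on which clause the assessor applies.

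**Step 3. Rough size.** Assumptions, none from the article: items independent; each improves with probability p = 0.50 in one arm and 0.65 in the other; 133 per arm; a share s of patients has one or two items fixed by entry status.

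- All four items open: P(≥3 of 4) = 4p³(1−p) + p⁴ = 0.3125 v 0.5630, difference 0.2505.
- Gasometry credited automatically: P(≥2 of 3) = 3p²(1−p) + p³ = 0.5000 v 0.7183, difference 0.2183.
- Auscultation cannot improve: p³ = 0.1250 v 0.2746, difference 0.1496.
- Gasometry and hematometry both credited automatically (extreme case): P(≥1 of 2) = 1 − (1−p)² = 0.7500 v 0.8775, difference 0.1275.

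Overall difference = (1−s) × 0.2505 + s × (difference in the affected group). For example, with s = 0.6 and the extreme case: 0.4 × 0.2505 + 0.6 × 0.1275 = 0.177.

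| Affected share s | 0 | 20% | 40% | 60% | Power at s = 0 → 60% |
|---|---|---|---|---|---|
| Gasometry credited | 25.0 | 24.4 | 23.8 | 23.1 points | 98.7% → 96.9% |
| No crackles at entry | 25.0 | 23.0 | 21.0 | 19.0 points | 98.7% → 92.9% |
| Gasometry and hematometry credited | 25.0 | 22.6 | 20.1 | 17.7 points | 98.7% → 86.6% |

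Power is for a two-sided 5% comparison of two proportions. The contrast shrinks in every scenario and vanishes in none.

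**The case against.** Several points on the other side stand.

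- A reader might infer that the day-5 rules as a whole ignore baseline. They do not. Auscultation and X-ray are judged against the earlier grade, and hematometry against a drop. Only gasometry uses a fixed cut.
- A reader might infer that patients are misclassified whatever the treatment does. Fixed credit reaches at most two of four items, so at least one other item must truly improve. With blinding, and randomization stratified by severity within hospital, the expected result is dilution rather than bias towards one arm.
- For patients who enter below 300, reaching 300 means that an entry sign has resolved. That is a legitimate, if strict, responder rule.
- Scoring no change as worsening for crackles and infiltrate, but as improvement for hematometry, is not in itself a contradiction. A persisting infiltrate is non-response, while a stable hematocrit means no further fall.
- Discharge before day 5 cannot be counted as a stated failure. The article does not address it, and a full protocol or SAP would normally do so.
- One could assume a 0.7 chance of improvement per item and show response rates from 34% to 78% by entry signs. That compares hypothetical patient types, not arms, and says nothing about how common they are.

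Two objections stand only in part. Crackles are graded once found, so the article may simply be silent on patients without them; the auscultation point therefore rests on a literal reading. The hematometry clauses can be separated if unchanged means no rise despite transfusion, but a patient already at an acceptable level when transfused still fits both. The gasometry rule, by contrast, is stated in full and does what Step 1 shows.

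**Conclusion.** The point holds for specific groups: patients entering at or above 300, those whose ratio rises substantially but stays below 300, those without crackles (on the literal reading), and those transfused and held at an unchanged acceptable level. For them, the classification depends on entry signs or on the assessor's choice of clause. The likely consequence is a weaker contrast and some discretionary scoring in a secondary outcome.

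Under the assumptions in Step 3, with up to 60% of patients affected, the difference falls from 25.0 points to 23.1 (gasometry alone), 19.0 (no crackles) or 17.7 (extreme case). The article does not give the share affected, and independence is doubtful because the items describe the same lungs, so these figures show only the order of size. Mortality and its 133 per group are unaffected. The definition should be corrected, but the trial's main conclusion does not depend on it.

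**What to change.** 1. Define the gasometry item as change from the patient's own pre-infusion PaO2/FiO2, with a prespecified rule for patients already at or above 300.
2. State how an item that is normal both at entry and on day 5 enters the count. One option is to score it as not assessable and require improvement in a fixed proportion of the assessable items. Write the threshold as a count: with three assessable items, a 75% threshold would still demand all three, since 2/3 = 67%. Neither choice matches 3 of 4 exactly. At p = 0.50, 3 of 3 gives 12.5%, 3 of 4 gives 31.3% and 2 of 3 gives 50.0%, so the choice must be made before unblinding.
3. Reconcile the two hematometry transfusion clauses so that no patient can meet both, and define the acceptable level.
4. Optionally, add a baseline-adjusted analysis (ANCOVA) of day-5 PaO2/FiO2 as supportive, with a stated rule for deaths before day 5, which matter when control mortality is expected to be 30%. It cannot replace the item inside a responder count.

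The cost is a slightly longer outcome definition. Assessments are already daily to day 7, so no new measurements are needed.
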